##### Secondary outcomes

3.12.2.2

Secondary outcomes are analyzed using repeated measures mixed linear models. Measures collected annually (months 0, 12, 24, 36, and 48) include KOOS pain, 6-min walk distance, SF-36 physical and mental subscales, weight loss self-efficacy, and exercise self-efficacy. Knee compressive force (baseline N ​= ​660) and IL-6 (baseline N ​= ​910) are measured at baseline and 48 months at two and three centers, respectively. The treatment effect for log-adjusted IL-6 is estimated using analysis of covariance adjusted for baseline log IL-6, baseline BMI, and clinical center and tested at a two-tailed 0.05 Type I error rate. Each repeatedly measured outcome treatment effect is modeled and tested using a two-tailed significance level of 0.05 using contrast statements from a repeated measures mixed linear model with time, randomization arm (D ​+ ​E vs C), and the group ​× ​time interaction, which adjusts the means at each time point for potential missing data bias. Intervention-effect estimates are adjusted further for baseline values of each outcome, baseline BMI, and center; the analysis will match design, so the variance estimate will not be biased. Outcomes at 48 months are of primary concern, with secondary consideration of other time points. An unstructured covariance matrix is used to account for the correlation between repeated outcomes. In the unlikely event the model does not converge, a first-order autoregressive (AR [1]) covariance structure is fit instead [61]. Maximum-likelihood techniques estimate parameters. Preliminary analyses check the shape of the distributions and variances between groups and as a function of the covariates of the prespecified models. Regression diagnostics and residual plots help to find appropriate transformations.

Sensitivity analyses will account for missing data in accordance with the recommendations of the National Research Council [62]. Models will include variables from previous visits determined to predict loss to satisfy Little and Rubin's [63] conditions for data considered missing at random (MAR). If “informative censoring” occurs, comparisons using subjects with complete data, multiple imputation, or explicit modeling of the censoring mechanism are used [63].

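### If the unstructured mixed model fails to converge, the only named fallback, AR(1), understates the 48-month standard error when residual variance rises over follow-up

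*Protocol article*

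**What the plan says.** Section 3.12.2.2 (Secondary outcomes) sets out a repeated-measures mixed linear model with visit, arm and their interaction for KOOS pain, 6-minute walk distance, the SF-36 subscales and the two self-efficacy scales.

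- **Target visit:** "Outcomes at 48 months are of primary concern, with secondary consideration of other time points".
- **Adjustment:** "Intervention-effect estimates are adjusted further for baseline values of each outcome, baseline BMI, and center". The same sentence adds that "the analysis will match design, so the variance estimate will not be biased".
- **Covariance:** "An unstructured covariance matrix is used to account for the correlation between repeated outcomes".
- **Fallback:** "In the unlikely event the model does not converge, a first-order autoregressive" structure takes its place. No other structure is listed.
- **Estimation:** "Maximum-likelihood techniques estimate parameters". The type of standard error is not stated.

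The preliminary checks on variance look between groups and across covariates. Visits are not named, and the stated response to diagnostics is a transformation of the data.

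**The concern.** An unstructured matrix gives month 48 its own variance. Standard AR(1) gives all visits one pooled variance. If the residual variance at month 48 exceeds that pool, the model-based standard error of the 48-month contrast is too small, and the test exceeds its nominal 5%.

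Two things can raise the residual variance over visits:

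1. The spread of the outcome itself grows over follow-up.
2. The spread is constant, but the baseline value, which is a covariate, predicts later visits less well than earlier ones. The adjustment then removes less variance at month 48 than at month 12.

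The statement that the variance estimate will not be biased belongs to the sentence on covariate adjustment. It does not protect against either mechanism once the fallback is in use.

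**Working it through.** **The plan's own figure.** Section 3.13 gives a detectable effect of 0.191 at 85% power with 492 evaluable per arm. (1.960 + 1.036) × √(2/492) = 2.996 × 0.0638 = 0.191, so it reproduces. For KOOS pain, 18.5 × 0.191 = 3.53, against 3.54 in Table 6. These figures come from a two-sample *t*-test and do not depend on the fallback.

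**Set-up for the check.** The responses are the four follow-up visits (12, 24, 36 and 48 months), with arm-by-visit means and baseline as a covariate. Data are complete. All correlations and relative standard deviations (SDs) below are assumptions, because the article gives only one SD of change per outcome (Table 6).

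**Formulas.**

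- At constant raw SD of 1, the residual variance at a visit after baseline adjustment is 1 − r², where r is that visit's correlation with baseline.
- AR(1) is fitted to the residual covariance by minimising the expected Gaussian −2 log-likelihood, which gives a pooled variance s².
- With complete data the 48-month contrast is the adjusted difference in means at that visit. The ratio of model-based to true standard error is therefore √(s² / residual variance at month 48), and the sample size cancels.
- Type I error = 2 × [1 − Φ(1.96 × ratio)].

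**Worked case.** Correlation is 0.65 at a lag of one year and falls by 0.05 per further year, at constant SD. Correlations with baseline are 0.65, 0.60, 0.55 and 0.50, so the residual variances are 0.578, 0.640, 0.698 and 0.750. The fitted s² is 0.666. The ratio is √(0.666/0.750) = 0.942. The error is 2 × [1 − Φ(1.847)] = 6.5%.

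| Assumed structure, baseline-adjusted | Ratio | Type I error |
|---|---|---|
| Constant SD, flat 0.6 | 1.000 | 5.0% |
| Constant SD, 0.60 falling 0.04 per year | 0.958 | 6.0% |
| Constant SD, 0.65 falling 0.05 per year | 0.942 | 6.5% |
| Constant SD, 0.70 falling 0.05 per year | 0.932 | 6.8% |
| Constant SD, true AR(1) with 0.7 | 0.899 | 7.8% |
| SD rising 1 to 1.25 (months 12 to 48), flat 0.6 | 0.903 | 7.7% |
| SD rising 1 to 1.25, 0.65 falling 0.05 per year | 0.859 | 9.2% |
| SD rising 1 to 1.25, AR(1) correlation 0.7 | 0.829 | 10.4% |

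**Is slow decay the cause?** Without baseline adjustment, every constant-SD structure in the table gives a ratio of exactly 1.000, whether correlation decays slowly, quickly or not at all. With adjustment, flat correlation still gives 1.000 and faster decay is worse. The driver is rising residual variance.

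**Attrition.** At the planned 5.4% per year and without baseline adjustment, SD rising to 1.25 gives a ratio of 0.90 and an error of 7.6–7.9%. Constant variance with flat correlation gives 1.001–1.013, which is slightly conservative.

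**The case against.** The strongest reply is that one named fallback, triggered mechanically by non-convergence, is common practice. An unstructured matrix for four visits has 4 × 5 / 2 = 10 parameters, against about 1,000 participants (2 × 492 = 984 evaluable at 48 months), so the article is right to call the event unlikely. The primary outcome uses a different model, IL-6 uses analysis of covariance, and the power figures are untouched. All of this stands and limits the weight of the point.

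It can also be said that the article writes neither an equal-variance AR(1) nor model-based errors, and that such details are often left to an analysis plan. That is fair as to the standard error. The choice of AR(1), however, is stated, and equal variance is its usual meaning.

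A reader might infer two stronger claims that the document does not support:

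- **That slowly decaying correlation in itself makes the standard error too small.** The calculation shows that it does not.
- **That the fallback is likely to be used**, because month 0 is listed among the visits while baseline is also a covariate, which would make the unstructured fit singular. The ordinary reading is follow-up responses with baseline as a covariate. If month 0 were kept in the response, the defect would lie in the mean model, and a different fallback would not cure it.

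**Conclusion.** The point holds in a narrow form. It needs four conditions together: the unstructured model fails to converge, AR(1) is used with equal variances, its errors are model-based, and residual variance rises towards month 48. Under the assumed covariances, the 48-month standard error is then about 4–10% too small at constant SD with fading baseline correlation (type I error about 6–8%), and about 10–17% too small if the SD also grows by a factor of 1.25 (about 8–10%). With flat correlation and constant SD there is no error. Since the article supplies no covariance values, these figures show a plausible range and do not predict what will happen in this trial. It is a minor improvement to the secondary analyses and does not threaten the trial's main conclusion.

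**What to change.** Replace the AR(1) sentence with a fixed order of structures that let the variance differ by visit, for example heterogeneous Toeplitz, then heterogeneous AR(1) or heterogeneous compound symmetry. State that an empirical (sandwich) variance is used whenever the unstructured model is not. The cost is one sentence in the analysis plan and a slightly wider interval when the fallback applies. Sample size and power statements need no change.

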### Sample size and power calculations

3.13

Sample size calculations used data from the Osteoarthritis Initiative (OAI) Biomarkers of Early Arthritis of the Knee (BEAK) dataset ([name], PI). The BEAK study examined MRI parameters including semi-quantitative MOAKS scores (Table 4) among a subgroup of radiographic OA-free (KL ​= ​0, 1) and MRI OA-free participants in the OAI cohort [64]. Participants were randomly selected from 2987 OAI participants who had at least one knee at risk for radiographic OA at baseline. MRI-based OA (MRI-OA) incidence was determined using the definition of Hunter et al. [19] to identify participants without MRI-OA at baseline and to estimate progression to MRI-OA using Poisson regression. Among all subgroups (age x sex x BMI), women aged ≥50 ​yrs with a BMI ≥30 ​kg/m^2^ were at highest risk for MRI-OA. This subgroup of women progressed to MRI-OA at a rate of 7.6 ​% (95 ​% CI: 4.2 to 13.8) annually while all potential subgroups of men averaged ≤5 ​% annually. Hence, women aged ≥50 ​yrs with a BMI ≥30 were most likely to benefit from a prevention study. Cumulatively, 27.1 ​% of the control knees in TOPS are predicted to progress to MRI-based structural knee OA by 48-month follow-up. A post hoc analysis of the PROOF data showed that participants that achieved a ≥5 ​% weight loss during the first year had a 67 ​% risk reduction in symptomatic and radiographic OA at 6-year follow-up compared to those with minimal weight loss or gain [65]. Using these estimates, a 30 ​% reduction in OA risk using a 48-month dietary weight loss and exercise intervention compared to control with 80 ​% retention (5.4 ​% attrition/year) requires 615 participants per arm (492/arm evaluable), or 1230 total, to achieve 85 ​% power based on a 2-tailed chi-squared test at the 0.05 level.

For secondary outcomes, this sample size provides the ability to detect a small to moderate treatment effect size of 0.191 (Cohen's d) at 85 ​% power (N ​= ​615, with 492 (80 ​%) evaluable at 48 months) using a 2-tailed *t*-test with a Type I error rate of 0.05. This degree of retention results in 85 ​% power to detect the group differences observed in Table 6. Significant treatment effect estimates are compared to clinically meaningful thresholds for each outcome when available to ensure both statistical and clinical significance.

**Table 6 tbl6:** Based on N ​= ​615/arm, 2-tailed alpha ​= ​0.05, 80 ​% retention at 48 months.

Variable	SD of Change from Baseline	Detectable treatment effect for 85 ​% power
KOOS Total Score^a^	17.0	3.25
KOOS Pain	18.5	3.54
6-Minute Walk Distance (m)	75	14.3
SF-36: Physical Subscale^b^	8.7	1.7
TF Compressive Force (Newtons)^c^ (N ​= ​269/arm)	290	84.0
Log-IL6 (N ​= ​492/arm)^d^	0.6	0.13
Weight Loss Self Efficacy	15	2.9
Exercise Self Efficacy	28	5.3

a KOOS: The Knee Injury and Osteoarthritis Outcome Score.

b SF: Short Form Survey.

c TF: Tibiofemoral.

d IL-6: Interleukin 6.

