### Randomization and masking procedures

3.3

Each eligible participant is randomized with a 1:1 allocation ratio to either a dietary weight loss, exercise, and weight-loss maintenance intervention or a control group using a permuted block randomization approach with random block sizes and stratified by intervention site to ensure balanced allocations within sites and obesity categories. A web-based randomization system will determine group assignment. Outcome assessors will remain blinded throughout the trial with no access to participants during intervention visits.

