**Additional Tests/Imaging**		
Height	To determine BMI	0
Weight	To determine BMI	0, 12, 24, 36, 48
Urine biomarkers^c^	Stored for subsequent analysis	0, 48
Knee PA, Sunrise x-rays	Screen for initial eligibility to undergo MRI exam	0
DXA^d^	To measure changes in body composition and BMD	0, 24, 48

a Methodology for knee joint loading and IL-6 measures can be found in our previous studies [12,20].

b Measured at the 3 US sites (N ​= ​910).

c Measured at the Winston-Salem and Chapel Hill sites (N ​= ​660).

d Measured at the Winston-Salem site (N ​= ​360).

To reduce biomechanical gait variability, a designated tester at each gait testing site (Wake Forest and UNC sites) will assume responsibility for the collection of gait data. To ensure the precision of marker placement and reliability between both sites, test-retest comparisons will be conducted during the 3-month planning period utilizing the same participant with obesity. Furthermore, the Bell regression equation set will be employed to facilitate a more accurate estimation of hip joint centers in participants with obesity [52,53]. All data analyses will be centralized at the Wake Forest location.

Additional measurements that are not included in the specific aims are height and weight, body composition, and questionnaires to assess eligibility, demographics, psychosocial outcomes, social determinants of health, dietary intake, additional KOOS subscales, and adverse events (Table 5).

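### Table 6: the knee-force detectable effect (84.0 N) and the IL-6 sample size (492/arm) do not fit the 660 and 910 participants in whom these outcomes are measured

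*Protocol article*

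**What the plan says.** Section 3.13 gives one general basis for the secondary outcomes: 615 randomized per arm, "with 492 (80 ​%) evaluable at 48 months", 85% power, "using a 2-tailed *t*-test with a Type I error rate of 0.05", and a standardized effect of 0.191. The Table 6 caption repeats 615/arm and "2-tailed alpha ​= ​0.05, 80 ​% retention at 48 months".

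Two rows of Table 6 carry their own sample size:
- "TF Compressive Force (Newtons"): 269/arm, SD 290, detectable effect 84.0.
- Log IL-6: 492/arm, SD 0.6, detectable effect 0.13.

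Elsewhere the article restricts both measurements to some centers. Section 3.12.2.2 gives baseline numbers of 660 for knee compressive force and 910 for IL-6, which "are measured at baseline and 48 months at two and three centers, respectively". The Table 5 footnotes agree: gait is "Measured at the Winston-Salem and Chapel Hill sites" (660) and blood is "Measured at the 3 US sites" (910). The recruitment goals in section 3.9.1 give the same totals: 360 + 300 = 660 and 300 + 360 + 250 = 910. Section 3.3 states that participants are "randomized with a 1:1 allocation ratio".

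**The concern.** A detectable effect is fixed by the evaluable number per arm, the SD, the error rate and the power, so each row of Table 6 should follow from its own entries and from the subset described elsewhere. The knee-force row does not follow from its printed sample size, and the IL-6 row prints more participants than will have blood drawn.

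These are planning figures for two of the three mechanistic pathways in the trial's model. Section 3.13 says that significant effects will be compared with clinically meaningful thresholds where these exist, so readers will use the detectable differences as a guide to what the trial can show. Taken at face value, the IL-6 row implies that IL-6 is measured across the whole trial, and the knee-force row makes the gait comparison look less sensitive than it is.

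**Working it through.** **Method.** Two-sample comparison of means, two-sided alpha 0.05, 85% power. To a close approximation,

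detectable effect = (1.960 + 1.036) × SD × √(2/n), with n evaluable per arm.

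The figures below use the exact t-test version (noncentral t), which is slightly larger.

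**Step 1: reproduce the full-sample rows.** At n = 492 the standardized effect is 0.191, as stated. Multiplied by each SD:

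| Row | SD | Computed | Printed |
|---|---|---|---|
| KOOS total | 17.0 | 3.25 | 3.25 |
| KOOS pain | 18.5 | 3.54 | 3.54 |
| 6-minute walk | 75 | 14.3 | 14.3 |
| SF-36 physical | 8.7 | 1.66 | 1.7 |
| Weight-loss self-efficacy | 15 | 2.87 | 2.9 |
| Exercise self-efficacy | 28 | 5.35 | 5.3 (0.191 × 28 = 5.348) |

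All six agree to rounding, so the method is the one that was used. The two remaining rows are the two that print their own sample size.

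**Step 2: knee force, SD 290.** The planned evaluable number is 660 / 2 × 0.80 = 264 per arm.

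| n per arm | Where it comes from | Detectable at 85% power | Power for 84 N |
|---|---|---|---|
| 269 | printed, read as evaluable | 75.1 N | 91.8% |
| 264 | 660 with 80% retention | 75.8 N | 91.3% |
| 330 | 660 with no loss | 67.7 N | 96.0% |
| 215 | 0.80 × 269 = 215.2 | 84.0 N | 85% |

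By the approximate formula at 264: 2.996 × 290 × √(2/264) = 75.6 N.

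The printed 84.0 N appears only at about 215 per arm. That is 430 in total, or 430/660 = 65% of the gait sample, against the 80% in the caption.

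**Step 3: log IL-6, SD 0.6.** The planned evaluable number is 910 / 2 × 0.80 = 364 per arm.

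| n per arm | Where it comes from | Detectable at 85% power |
|---|---|---|
| 492 | printed, read as evaluable | 0.115 |
| 364 | 910 with 80% retention | 0.133, prints as 0.13 |
| 394 | 0.80 × 492 | 0.128, prints as 0.13 |

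The printed sample size means 2 × 492 = 984 participants, which is 74 more than the 910 measured at baseline, so no retention rate can produce it. At 364/arm, power for exactly 0.13 is 83.1%; for the unrounded 0.133 it is 85%. Any n from about 356 to 414 per arm gives an effect that prints as 0.13, so the rounded figure does not show which n the authors used.

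**The case against.** The strongest defense is that both rows reproduce under a single convention. If the printed sample size is taken before attrition and the caption's 80% retention is applied, 269 becomes 215 and gives 84.0 N, and 492 becomes 394 and gives 0.128, printed as 0.13. On that reading the rows are internally consistent, and a reader who infers that the table mixes randomized and evaluable numbers goes further than the article supports. That part of the defense stands. The convention still does not rescue the entries: as pre-attrition totals, 2 × 269 = 538 is not 660, and 984 is not 910.

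A second defense is that 269 is close to the expected evaluable 264 (1.9% apart), so the knee-force sample size may be sound and retention may simply have been applied twice. That is possible. The article supports neither this nor the view that 269 is a randomized number, so the cause stays open.

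A reader might also infer that the 85% power figure is wrong for both outcomes. For IL-6 it is not: with the 364/arm that the design delivers, 0.13 is correct to the printed precision.

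Finally, the consequences are small. These are secondary outcomes, the trial is sized on the MRI endpoint, and the knee-force figure errs on the cautious side. All of this stands and sets the weight of the point, but the printed figures still need correcting.

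**Conclusion.** Two entries in Table 6 are wrong as written, and the matter is minor.

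- Knee force: 84.0 N does not follow from 269/arm evaluable or from 660 with 80% retention. The design gives about 75.8 N, so the printed value is 8.2 N (about 11%) too large. At 264/arm the trial has about 91% power for 84 N, so the error is conservative.
- Log IL-6: 492/arm cannot be obtained from 910 participants. The evaluable number is 364/arm, which is 128 fewer (26%). The detectable effect of 0.13 stands.

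This rests on the article's own SDs, equal allocation within the measuring centers, and the 80% retention in the caption applying to gait and blood as it does to the trial as a whole. The two inconsistencies do not depend on the retention assumption: 269 evaluable per arm does not give 84.0 N, and 984 exceeds 910. No underpowering is shown for either outcome, and the primary analysis and its sample size are untouched.

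**What to change.** Restate both rows of Table 6 as evaluable numbers per arm:
- Knee compressive force: 264/arm (660 × 0.80 / 2), detectable effect 75.8 N. If 84.0 N was meant to rest on a different gait sample or a lower completion rate, state it and reconcile it with the 660 in Table 5 and section 3.12.2.2.
- Log IL-6: 364/arm (910 × 0.80 / 2), detectable effect 0.13.

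Add to the caption that these two rows rest on the 660 and 910 subsets and not on 615/arm. The cost is a table correction, with no change to the design, the sample size or the analysis.

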## Discussion

4

Implementing a randomized clinical trial designed to prevent incident knee OA presents numerous challenges. OA disease status and severity are defined structurally via x-ray [36] or MRI [19] and clinically using a combination of symptoms reported by the patient and derived from a physical exam [66]. The primary outcome measure for TOPS is structural knee OA using MRI, due to its superior sensitivity and granularity compared to radiographic assessments. In addition, the use of radiographic assessments as the primary outcome measure to determine the presence or absence of incident knee OA would have increased the sample size by 478 participants (39 ​%), requiring additional clinical centers and greater costs to test the hypothesis effectively.

Losing weight and preventing weight regain are difficult [67]. Biological changes fight attempts to maintain weight loss; the body acts in starvation mode increasing feelings of hunger, satiety is suppressed, metabolic rate slows, all in an attempt to defend higher body weights [68]. Psychosocial obstacles include decreased self-efficacy, increased chronic perceived psychosocial stress, and using food for comfort; environmental obstacles include large food portions and food availability [69]. Our previous work provides encouragement that most of the weight-loss attained by the TOPS diet and exercise group can be retained long-term with implementation of the weight-loss maintenance program. In a subsample of the IDEA cohort (N ​= ​94), the diet-only group retained 5.8 ​kg (65 ​%) of an 8.9 ​kg weight loss 3.5 years following completion of the 18-month diet intervention [70]. Maintenance of this clinically important weight-loss occurred without any post-intervention interaction with the study staff.

A limitation of this study is the exclusion of male participants. This was based on a preponderance of data that places females at nearly twice the risk for incident knee OA than males [18]. Furthermore, the estimated lifetime risk of knee OA for people with obesity is 16 ​% for males and 24 ​% for females [71]. There are also sex differences in OA symptoms - worse in females [72,73], cartilage volume - females have less cartilage and more cartilage volume loss [74], knee laxity - females have greater knee laxity [75], hormonal influences – decreased estrogen after menopause [76,77], and gait differences – greater knee kinetics linked to more tibiofemoral compartment loading [78]. Taken together, these differences place females at greater risk for the development of knee OA. Additionally, the inclusion of males would have increased the sample size by 32 ​%, required additional clinical centers, increased costs substantially, and added to the logistical complexities managed by coordinating center staff.

The PROOF clinical trial was an initial attempt at implementing a trial designed to prevent incident knee OA. The rate of incident knee OA was not different between the diet and exercise (N ​= ​101) and control (N ​= ​102) groups after a 2.5-year intervention period. A low adherence rate (28 ​%), however, resulted in only 15 ​% of the diet and exercise group achieving a 5 ​% weight loss [38]. A post-hoc analysis revealed that participants who did achieve the 5 ​% weight loss goal by the end of the first year reduced the risk of symptomatic and radiographic knee OA by 67 ​% at 6-year follow-up compared to those with minimal weight loss or weight gain in year one [65]. The use of a social cognitive conceptual framework for implementing problem-solving strategies and structuring a positive environment designed to improve adherence and retention [30], a larger sample size, a 4-year intervention period with a weight-loss maintenance program built-in, and a 10 ​% weight-loss goal are design improvements that are being implemented in the current trial.

The importance of OA disease prevention is evident because there are presently no effective disease-modifying interventions, there are substantial safety concerns associated with many pain medications, and there is no cure. TOPS will evaluate a critically needed primary prevention intervention on females at risk for the development of knee OA by implementing a program of dietary weight loss, exercise, and weight-loss maintenance designed for long-term sustainability to maximize health benefits at a reasonable cost.

